In the current pandemic, the impact of quarantine and physical distancing on the mental health of the general population has been explored only in a few studies, mostly conducted in China, where the pandemic started (23–25). Qiu et al. (26) found that 35% of the population experienced psychological distress; in particular, those more vulnerable to stress and more likely to develop post-traumatic stress disorder were women and individuals aged between 18 and 30 years or older than 60 years. Moreover, people were more concerned about their own health and that of their family members, while less concerned about leisure activities and relationships with friends (24, 27).

After China, Italy has been the first country to face the contagion of COVID-19 and one of the countries with the highest number of deaths due to this coronavirus (http://www.salute.gov.it/portale/nuovocoronavirus/). On March 8, the lockdown status has been declared by the Italian government. This status included the definition of specific containment and quarantine measures, such as the interdiction of all public meetings and strict movement restrictions (i.e., possibility to go out only for working, serious health reasons, or other urgent needs). These containment measures have been prolonged until May 4.

Moreover, the expected psychosocial and emotional reactions to the pandemic observed in the general population may be significantly different in the Chinese and Italian populations due to their socio-cultural characteristics and historical contexts, which obviously impact on people’s behaviors and attitudes. Furthermore, the organization of public health system is different in Italy compared to China and other Eastern Asian countries, also due to financial constraints. In fact, although in those countries the model of care has shifted in the last 20 years to become more similar to a Western model of care, it has to be acknowledged that 20 years is a relatively short period of time, and differences may still persist.

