#### Exploratory Outcomes

The use of Internet and social media will be tested as possible moderator of the impact of pandemic and quarantine (**Figure 1**). Moreover, the exposure time to COVID-19 and to the related containment measures will be tested as possible mediators of the severity of the clinical symptomatology. Finally, the other exploratory outcomes will include the variety of coping strategies and resilience styles as well as the different levels of post-traumatic growth.

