### Data Analysis

Statistical analyses will be conducted according to a multistep plan. Missing data will be handled using the multiple imputation approach (47). Descriptive statistics will be calculated for the dependent and confounding variables. A bilateral alpha of 0.05 is considered, and error and confidence intervals are calculated at 95%.

The analytic plan will include: 1) data cleaning of the online dataset and replacement of missing values; 2) descriptive statistics of the general characteristics of the recruited sample, in terms of levels of depressive and anxiety symptoms, post-traumatic and stress-related symptoms, insomnia, satisfaction with life, suicidal ideation, hopelessness, post-traumatic growth, resilience, coping strategies, and social support; 3) sub-groups analyses based on the level of exposure to the pandemic (i.e., COVID-19 quarantine group vs. COVID-19+ patients group vs. COVID-19 healthcare staff group vs. COVID-19 mental health group); 4) calculation of a propensity score, in order to adjust our findings for the likelihood of being exposed to the pandemic and to the quarantine (48, 49). This method is adopted since it produces a better adjustment for differences at baseline, rather than simply including potential confounders in the multivariable models. The independent variables used for calculating the propensity score will include gender, age, socio-economic status, and geographical region. The obtained propensity score will be used to weight the observations in the multivariable analyses. In the final regression model, the inverse probability weights, based on the propensity score, will be applied in order to model for the independence between exposure to the pandemic/quarantine and mental health outcomes and estimation of causal effects (48, 49); 5) development of a Structural Equation Model (SEM), in order to evaluate the possible role as mediators and moderators of coping strategies, post-traumatic growth and usage of social networks on the severity of depressive and anxiety symptoms, post-traumatic and stress-related symptoms, suicidal ideation, and hopelessness.

In order to improve the external validity and generalizability of our findings, all analyses will be controlled for the impact of confounding variables, such as age, gender, and geographical region.

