Another possible limitation of our study is the choice to use a web-based online survey, which may have limited the participation of people not having access to the Internet or not familiar with online tools, particularly the elderly. The cross-sectional design of the study does not allow an evaluation of changes over time as regards the levels of severity of symptoms. However, in order to overcome this possible bias, we will compare our findings with those already available from the Italian population (46) and will adopt a propensity score approach in order to understand the impact of the duration of exposure to the pandemic on the risk of developing psychiatric symptoms. With this methodology, we will be able to evaluate the levels of post-traumatic growth and the type of resilience styles in the study population in order to identify possible critical areas to be targeted in the post-acute phase. However, these psychological constructs are slow to change, and this is why we will promote a second wave of the survey, which will start six months after the end of the “lockdown phase” in Italy. Finally, the survey link can be used multiple times in order to allow sharing and re-posting it. This methodological choice could bias the findings, since the same person can potentially compile the survey several times. However, this methodological choice was due to the adoption of the “snowball” sampling, and it is rather unlikely that someone can compile the same long survey more than once.

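### The exposure named for the propensity score is the same for every respondent, so the weights cannot give the causal effect of pandemic or quarantine; the article also names different exposures for the same score

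*Protocol article*

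**What the plan says.** In the protocol article, step 4 of Data Analysis sets out a propensity score "in order to adjust our findings for the likelihood of being exposed to the pandemic and to the quarantine". On its inputs it says: "The independent variables used for calculating the propensity score will include gender, age, socio-economic status, and geographical region". The resulting inverse probability weights go into the final regression, whose purpose is given as "independence between exposure to the pandemic/quarantine and mental health outcomes and estimation of causal effects".

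Other places bear on what the exposure is:

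- Data Analysis, step 3, plans "sub-groups analyses based on the level of exposure to the pandemic" and lists the four study groups as those levels.
- Discussion (limitations) says the authors will "adopt a propensity score approach in order to understand the impact of the duration of exposure to the pandemic". It offers this, together with a comparison against earlier Italian data, as the answer to the cross-sectional limitation.
- Exploratory Outcomes says that "the exposure time to COVID-19 and to the related containment measures will be tested as possible mediators of the severity of the clinical symptomatology".
- Background: "On March 8, the lockdown status has been declared by the Italian government", with the measures extended to May 4.
- Recruitment Procedure has the survey online from March 30 to June 30, 2020, and defines Group 1 as people in quarantine but not in isolation.
- The opening of the Discussion defines Group 4 by mental health problems, whatever the person's contact with the virus.

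**The concern.** A propensity score models the probability of receiving one exposure level rather than another. It needs people at each level within the data. For the exposure that step 4 names, no respondent can be at the unexposed level. The only unexposed people in the plan are an external Italian community sample (Primary Outcome), and the article does not say that their individual records enter the propensity model.

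The weighted regression is the only step that carries an explicit causal claim, and the first study aim is the impact of the pandemic and its containment measures. If the wording stands, differences among volunteers who were all exposed could be reported as the causal effect of the pandemic. Because the article assigns the score two exposures and suggests a third, two analysts could also follow the text and estimate different quantities.

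**Working it through.** The plan gives no figure to reproduce here, since the question is one of identification. The check has three parts.

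**1. Is anyone unexposed?** Dates are from Background and Recruitment Procedure.

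- March 8 to March 30 (survey opens): 30 − 8 = 22 days.
- March 8 to May 4 (measures end): 23 + 30 + 4 = 57 days.
- March 8 to June 30 (survey closes): 23 + 30 + 31 + 30 = 114 days.

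The minimum is 22 days, so nobody has zero exposure. Those answering after May 4 are no longer under the measures, but they have already had all 57 days of them. Two durations have to be kept apart:

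| Quantity | Range | Spread |
|---|---|---|
| Time under lockdown | 22 to 57 days | 35 days |
| Calendar time since March 8 | 22 to 114 days | 92 days |

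**2. What do the weights do under the literal wording?** Let E = 1 denote exposed and X the covariates. If E = 1 for all, P(E = 1 | X) = 1 and each weight is 1/1 = 1. The effective sample size, (Σw)²/Σw², equals n. In practice a logistic model with an all-ones outcome shows perfect separation and does not converge, as a trial fit confirmed.

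**3. What do they do if the four groups are the exposure?** This was simulated with n = 20,000. The group shares, coefficients and outcome model are assumptions for illustration, not estimates for this study. A multinomial score with stabilised weights gave:

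- weights from 0.23 to 5.95;
- effective sample size about 17,800 of 20,000;
- group means of standardised age moving from between −0.18 and 0.27 (unweighted) to between −0.02 and −0.01 (weighted).

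The weights therefore vary and do rebalance. A common pandemic effect D was then added to everyone's outcome:

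| D (points) | Intercept | Group 2 vs 1 | Group 3 vs 1 | Group 4 vs 1 |
|---|---|---|---|---|
| 0 | 10.06 | 1.90 | 1.03 | 5.76 |
| 5 | 15.06 | 1.90 | 1.03 | 5.76 |
| 10 | 20.06 | 1.90 | 1.03 | 5.76 |

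The whole of D goes into the intercept and the contrasts do not move. This follows algebraically from adding a constant, so it does not depend on the assumed coefficients. No within-survey contrast between groups carries information on pandemic versus none.

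A duration exposure would also vary between respondents; it was not simulated. Without respondents at zero days, reaching the no-exposure state means extrapolating below 22 days.

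**The case against.** The strongest reply is that step 4 should be read with its neighbours. Step 3, immediately before it, calls the four groups levels of exposure, and the Discussion ties the score to duration. Both vary, so the score can be fitted and the weights can do useful work. Much of this stands, and it rules out several stronger conclusions that a reader might draw:

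- *That the weighting adjusts nothing.* This holds only under the literal yes/no exposure. With groups as the exposure, the simulation shows weights that vary and balance covariates.
- *That the weighted result would equal an unadjusted one.* The last paragraph of Data Analysis controls all analyses for confounders such as age, gender and region. Constant weights would still leave a covariate-adjusted regression.
- *That the primary hypotheses cannot be tested.* Primary Outcome sets out a comparison with an external sample and differences between groups. Neither needs the degenerate contrast.
- *That calling exposure time a mediator would remove part of the effect.* Exposure time is an exploratory item, the structural equation model in step 5 does not name it, and nothing places it in the weighted regression. The label is loose, but the harm is speculative.
- *That prior mental disorder is simply missing from the score.* It defines Group 4. Putting it into a score across all four groups would itself break positivity, and the listed covariates are not clearly meant to be exhaustive.

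The choice of stabilisation, truncation and variance estimator can also fairly be left to an analysis plan.

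The reply does not rescue the text. The article states the exposure, the weighting and the causal aim, and these do not fit together. Step 3 and the Discussion offer two different replacements. The four groups are not a clean exposure scale either, because Group 4 is defined by diagnosis and Group 3 by occupation.

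**Conclusion.** The point holds in this form. As step 4 is worded, the exposure is constant (at least 22 days for every respondent), positivity fails, and the causal effect of pandemic or quarantine versus none cannot be estimated from the survey. The article also gives the same score different exposures in Data Analysis and in the Discussion. Reading the exposure as group or duration makes the weights workable but leaves pandemic versus no pandemic unidentified.

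This rests on the article's own dates and group definitions, and on the assumption that individual records from the external community sample are not pooled into the propensity model, since the article does not say that they are. The simulated weight range and effective sample size only illustrate that the weights need not be constant. It should be corrected before analysis, because it changes which causal statement the study can make.

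**What to change.** 1. In step 4, name one exposure contrast that varies within the sample: for example quarantined only versus contact or isolated, and first- versus second-line among staff.
2. Fit the propensity score that matches it, multinomial where there are more than two levels. Add response date. Include pre-existing mental disorder only where it does not define one of the compared groups.
3. If duration is studied, treat it as a dose, and separate time under lockdown (22 to 57 days) from calendar time since March 8 (22 to 114 days). Response date then determines the dose and cannot also serve as a covariate.
4. Restrict the causal wording in Data Analysis to the named contrast.
5. Delete the Discussion's suggestion that the propensity score overcomes the cross-sectional design. Describe the comparison with the community sample as an unweighted external comparison, unless its individual data are pooled.

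The cost is a narrower causal claim, revised wording and slightly more programming. It assumes that the response date and each respondent's contact or isolation status are recorded, which the article does not spell out.

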## Background

The ongoing COVID-19 pandemic represents an unprecedented event in terms of consequences for physical and mental health of individuals and for the society at large (1–4). In order to reduce the spread of the virus, national and international bodies and institutions have ordered quarantine, physical distancing, and isolation almost everywhere in the world. However, the psychological consequences of quarantine, such as frustration, loneliness, and worries about the future are well-known risk factors for several mental disorders, including anxiety, affective disorders, and psychoses (5–7).

From a medical and sociological viewpoint, the pandemic caused by COVID-19 represents a unique event, since it does not resemble any other previous traumatic event, such as earthquakes or tsunamis (8). In those cases, the traumatic factors are usually limited to a specific area and to a given time; affected people know that they can “escape” from the event. On the contrary, in the case of COVID-19 pandemic, the “threat” can be everywhere and can be carried by every person next to us (9–11). Therefore, people living in cities most severely impacted by the pandemic are experiencing extremely high levels of uncertainties, worries about the future and fear of being infected.

The only comparable studies are those carried out during the SARS outbreak (12–16). Those studies showed that people experienced fear of falling sick or dying, feelings of helplessness, increased levels of self-blame, fear, and depression (17–20). During quarantine and physical distancing, Internet and the social media can be useful in reducing isolation and increasing opportunities to keep in contact with family members, friends, and co-workers at any time (21, 22). However, Internet may also represent a risk factor for mental disorders, in particular Internet Gaming Disorder. Moreover, Internet can also have a negative impact on mental health of the most vulnerable people, such as those who live alone or the elderly, since it spreads an uncontrolled amount of information (a situation known as “infodemic”).

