Finally, the pandemic will affect the mental health status of people who already suffer from mental health problems, independently from the contact with the virus (COVID-19 mental health group). Although the effects of the coronavirus on mental health have not been systematically studied, it is likely that the COVID-19 will have detrimental effects on patients with pre-existing mental health problems. Many patients with severe mental disorders have been overlooked during the pandemic, although they can have a higher risk of contracting the virus and of death considering the higher prevalence of somatic comorbidities compared to general population and the difficulties in accessing health services (70).

However, if protracted, social isolation may increase the risk of recurrences of episodes of mental disorders, beyond triggering the onset of new mental disorders in most vulnerable people. Moreover, objective social isolation and subjective feelings of loneliness are associated with a higher risk of suicidal ideation and suicide attempts (71). For many persons with mental disorders, being alone is a heavy burden, far beyond that experienced by many other persons (72).

In patients with pre-existing anxiety disorders or obsessive-compulsive disorder, we expect an exacerbation or worsening of their clinical symptoms. Moreover, the fact that there is not (yet) a definitive treatment for the COVID infection represents another potential stressor, further increasing the levels of anticipatory anxiety and reducing personal functioning. In our study, both obsessive-compulsive and anxiety symptom clusters will be evaluated through reliable and validated questionnaires.

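### Weighting on four named variables supports neither the claim of better adjustment nor the causal wording

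*Protocol article*

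**What the plan says.** Step 4 of the Data Analysis section calculates a propensity score for exposure to the pandemic and quarantine. On its content: "The independent variables used for calculating the propensity score will include gender, age, socio-economic status, and geographical region". The stated reason for choosing this method is that "it produces a better adjustment for differences at baseline, rather than simply including potential confounders in the multivariable models". Inverse probability weights from the score go into the final regression model "in order to model for the independence between exposure to the pandemic/quarantine and mental health outcomes and estimation of causal effects".

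The section closes by saying that "all analyses will be controlled for the impact of confounding variables, such as age, gender, and geographical region". The three variables named there are already in the score.

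The data come from a cross-sectional online survey with snowball sampling, in which age is the only strict eligibility limit (Recruitment Procedure). The Discussion lists self-selection, Internet access, the cross-sectional design and repeat completion as limitations. It offers the propensity score as part of the answer to the cross-sectional design. It does not mention unmeasured confounding.

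**The concern.** Two affirmative statements go further than the method allows. The first is a general claim that weighting adjusts better than putting the confounders in the model. The second is that the weighted model estimates causal effects. Weights calculated from a set of variables balance that set. They act on anything else only as far as it is correlated with the set, and the same is true of regression on those variables. A causal reading therefore needs the assumption that nothing else drives both exposure and distress. The article does not state that assumption, and four demographic variables make it hard to accept.

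The primary hypothesis orders the groups on DASS-21 and includes two equalities. With more than 20,000 respondents expected, a modest residual bias could be reported as a significant effect of exposure.

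**Working it through.** **Inputs.** From the document: the four score variables, two-sided alpha of 0.05, and more than 20,000 respondents expected. The document gives no effect size, SD, prevalence or group size, so there is no figure of its own to reproduce. All such values below are assumptions.

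**Step 1. Size of the bias from one omitted binary factor.** In SD units, bias = effect of the factor x difference in its prevalence between the groups, given the measured covariates.

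- Smallest: 0.2 x 0.05 = 0.01 SD
- Middle: 0.3 x 0.10 = 0.03 SD; 0.4 x 0.30 = 0.12 SD
- Largest: 0.5 x 0.30 = 0.15 SD

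**Step 2. Does weighting remove more of it than regression?** Simulation with 400,000 records, true exposure effect zero, one measured covariate and one omitted binary factor (Monte Carlo error about 0.004):

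| Effect of factor (SD) | Prevalence difference | Bias, regression | Bias, weighting |
|---|---|---|---|
| 0.3 | 0.098 | 0.034 | 0.034 |
| 0.3 | 0.203 | 0.070 | 0.071 |
| 0.5 | 0.100 | 0.051 | 0.052 |
| 0.5 | 0.200 | 0.106 | 0.107 |

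The two methods agree to within 0.001 SD, and both lie within about 0.01 of the product in Step 1 (for example 0.5 x 0.200 = 0.100).

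**Step 3. Would a test notice?** For a contrast with no true difference, SE = sqrt(1/n1 + 1/n2), and the rejection probability is Phi(b/SE - 1.96) + Phi(-b/SE - 1.96), where b is the bias.

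| Assumed group sizes | SE | b = 0.03 | b = 0.06 | b = 0.12 |
|---|---|---|---|---|
| 15,000 and 500 | 0.0455 | 10% | 26% | 75% |
| 15,000 and 2,000 | 0.0238 | 24% | 71% | above 99% |
| 10,000 and 4,000 | 0.0187 | 36% | 89% | above 99% |

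These SEs ignore the weights. With 12,000 against 800 in a separate simulation, the SE was 0.037 for regression and 0.041 to 0.042 for weighting, so weighted rejection rates would be somewhat lower.

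**Step 4. Form of the age term.** The Background reports that the people more vulnerable to stress "were women and individuals aged between 18 and 30 years or older than 60 years". I raised distress by 0.2 or 0.4 SD at ages up to 30 and over 60, with exposure concentrated in working or middle age and no true effect.

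- One linear age term: regression left -0.034 to -0.089 SD, weighting -0.036 to -0.088 SD.
- Age bands: 0.009 SD or less under both.
- Exposure log-linear in age, linear term: regression left 0.003 to 0.020 SD, weighting at most 0.007 SD.

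In the last case the weight model is right and the regression is not, and weighting does slightly better.

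**The case against.** Several stronger readings are tempting, and the document does not support them.

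- **That the plan ignores a U-shaped age effect.** Age is in the score, and no linear term is stated. Its functional form is something an article may leave to the full plan. The age pattern also comes from one cited study, and the Background says the few such studies were mostly done in China and that reactions may differ in Italy. Step 4 supports a precaution; it does not show an error.
- **That the protocol names somatic illness as a driver of distress.** The Discussion cites "the higher prevalence of somatic comorbidities compared to general population" to explain infection and death risk in people with severe mental disorders. It makes no link to distress.
- **That living alone is an acknowledged confounder.** The Background names the most vulnerable, "such as those who live alone or the elderly", in a sentence about the Internet. That living alone changes the chance of belonging to the COVID-19+ group is plausible, but the document does not say so.
- **That the adjustment set is closed.** The wording of both lists leaves room for more variables.
- **That any such bias would be significant.** With 12,000 against 800, a bias of 0.035 is about one SE (0.035/0.037 = 0.95). Omitted factors may also act in opposite directions and partly cancel.
- **That weighting is never better.** Step 4 shows an exception. The plan also combines weighting with covariate control, so the two are not strict alternatives.

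All of this stands, and it narrows the point. It does not rescue the two claims. Combining weights with the same covariates adds no information about a factor in neither model. An open list does not turn the four named variables into a basis for causal effects.

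**Conclusion.** Wrong as written, for the superiority claim and the causal wording. For confounders outside the named set, weighting leaves the same bias as regression on the same variables; this result does not depend on the assumed sizes. The general statement that weighting adjusts better is therefore false, although it can hold in particular cases.

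The size of any bias cannot be derived from the document. On assumed inputs (effect 0.2 to 0.5 SD, prevalence difference 5 to 30 points) it is about 0.01 to 0.15 SD. The low end would usually go unnoticed. The upper end would often be declared significant in the larger contrasts. A reader should not infer that the planned contrasts are known to be biased by a given amount. The conclusion is that the analysis supports adjusted associations and cannot support more.

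**What to change.** In step 4 and the closing paragraph of Data Analysis:

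1. Delete the general claim that weighting adjusts better than covariates in the model.
2. Replace the aim of estimating causal effects with wording such as: *weighted results are associations between group and outcome, adjusted for the measured covariates; confounding by unmeasured factors cannot be excluded*. Add the same limitation to the Discussion.
3. State that age enters as bands (18-30, 31-60, over 60) or a spline in both the weight model and the outcome model.
4. Add living situation and other pre-exposure variables to both models where the ad hoc schedule already collects them.
5. Report a sensitivity analysis for unmeasured confounding, for example an E-value, for the primary contrasts.

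The cost is a weaker stated conclusion, a few degrees of freedom and a little extra analysis. New survey items are not a good substitute: the article reports 10,000 participants within 7 days, and answers to new items could not be recovered for people who had already responded.
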